#### 2.4.5. Blinding procedures

Due to the nature of Kneipp hydrotherapy and acupressure, patients and study physicians cannot be blinded. To minimize bias, all outcomes at baseline and 6 and 12 weeks after randomization will be evaluated by the same independent, experienced investigators blinded to the group assignment. After the completion of the statistical analyses, the group assignment will be announced by the research associate for biometrics.

#### 2.4.6. Randomization

Randomization will be performed centrally based on a computer-generated randomization list (generated using R software (version 4.1.2)) and will be block randomization with variable block length. Allocation to the 3 groups will be in a 1:1:1 ratio. Randomization will be performed at the end of the inclusion examination by the study physician using an administrative database. This will happen after informing about the study, providing written informed consent, and reviewing the inclusion and exclusion criteria. The last name, first name, date of birth, and sex will be entered into the administrative database by the study physician. The system performs automated randomization, and randomization confirmation is generated and printed using a button click. All further personal data will then be completed by the study nurse. The result of the randomization is communicated to the patients when the baseline questionnaires have been completed. Subsequently, training in the respective interventions will take place.

### 2.5. Sample size calculation

As this is an exploratory study to generate the first results and further queries about the effect of hydrotherapy and acupressure in patients with RLS, we did not make a sample size estimation. As we expect about 10% of the patients to drop out of the study before week 12; 17 randomized patients per group (51 randomized patients in total) are planned and seem logistically feasible at the study center. Thus, we expect to have at least 15 patients aged 18 to 75 years per group at week 6.

### 2.6. Attendance and drop-outs

The attendance of each patient is recorded by the return and evaluation of diaries and questionnaires. Dropouts and reasons for dropout will be recorded in the study database.

### 2.7. Statistical methods

All data collected are analyzed descriptively: means, standard deviation, median and quartile, or frequencies and percentages (overall and separated by intervention group). Endpoints are analyzed graphically and in an exploratory manner, and depending on the scale, performed using analysis of covariance or logistic regression (in each case, the treatment group and (if available and in case of relevant group differences) the respective baseline values are adjusted for as covariates). Adjusted means or odds ratios with 95% confidence intervals and p-values for the group comparisons are reported. All *P* values are considered exploratory without adjustment for multiple testing. Analyses are performed using the full analysis set, and the population is defined according to the intention-to-treat principle, that is, classification according to each randomization group, for patients with the data available for the respective evaluation. There will be no substitution for the missing data. Analyses are performed using statistical package for social sciences (SPSS) (IBM SPSS Statistics, version 25), R (version 4.1.2), and SAS (SAS for Windows, version 9.4).

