#### 2.4.4. Outcomes

Patients will receive the following questionnaires, which will be completed at baseline and 6 and 12 weeks after the start of the intervention phase:

*International Restless Legs Syndrome Study Group Rating Scale for Severity of Restless Legs Syndrome*^[50]^: 1 of 3 assessments which is validated for the German language area for the assessment of RLS severity and for the characterization of RLS

*Restless Legs Syndrome Quality of Life Questionnaire (RLS-QoL*)^[51]^: An 18-item scale to assess the quality of life of patients with restless legs syndrome.

*Quality of Life Short Form 12*^[52,53]^: general health questionnaire, which refers to 8 different dimensions that allow a statement about the health status of the patients.

*Hospital Anxiety and Depression Scale*^[54]^: assesses depression and anxiety severity in patients with somatic diseases or (possibly psychogenic) physical complaints.

*General Self-Efficacy Scale*^[55,56]^: A self-assessment procedure with ten items for recording general optimistic self-beliefs.

*Visual Analogue Scale*^[57]^: measures subjective general well-being on a visual analog scale (minimum 0 to maximum 100 mm).

*Patient Global Impressions Scale—Change*^[58]^ evaluates all aspects of the patient health status and assesses whether there has been improvement or deterioration in clinical condition.

We also want to investigate whether patients perceive a change in daily activities and how they estimate the effectiveness of the intervention before randomization, the success of the therapy, and the overall effectiveness of the interventions at the end of weeks 6 and 12.

In addition, the patients keep a diary to record the frequency of the study interventions and changes in their medication daily from week 1 to week 6. In the diary, patients will also note any side effects, adverse events, or serious adverse events. The first diary, which is handed out to the patients after randomization, is kept daily from weeks 1 to 6. The second diary is mailed to patients 12 weeks after enrollment, that is, at the end of the follow-up period, and is intended to retrospectively record the last 6 weeks of voluntary intervention, that is, safety, medication use, and continuation/frequency of intervention.

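### Baseline adjustment depends on observed group differences, which makes the model data-dependent and gives up precision on continuous outcomes whenever the baseline term is left out

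*Protocol article*

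**What the plan says.** Section 2.7 (Statistical methods) says that endpoints will be "performed using analysis of covariance or logistic regression", according to scale. Treatment group is always in the model. The baseline value is added under two conditions: "if available and in case of relevant group differences) the respective baseline values are adjusted for as covariates". The output is then described as follows: "Adjusted means or odds ratios with 95% confidence intervals and p-values for the group comparisons are reported". The p-values "are considered exploratory without adjustment for multiple testing".

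Section 2.4.4 (Outcomes) lists the questionnaires, "which will be completed at baseline and 6 and 12 weeks after the start of the intervention phase". For most scales, then, a baseline value exists and the second condition, observed group differences, decides.

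On size, section 2.5 says that "17 randomized patients per group (51 randomized patients in total) are planned", that "we expect about 10% of the patients to drop out of the study before week 12", and that "we expect to have at least 15 patients aged 18 to 75 years per group at week 6". No power, effect size or SD is given. Section 1.2 states that the results should support a confirmatory trial and its sample size calculation.

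**The concern.** Allocation is random, so any baseline difference between arms is due to chance. Baseline imbalance is therefore the wrong trigger. What makes a baseline value worth including is its correlation with the outcome, and that is present whether or not the arms happen to differ.

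Three consequences follow.

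- The model is settled only after baseline data by group have been examined, and it may differ from one endpoint to the next.
- When the baseline term is left out, treatment group is the only term. The ANCOVA is then a one-way ANOVA, and the means that section 2.7 calls adjusted are raw means. One results table could hold both kinds of estimate.
- On a continuous outcome, the unadjusted branch leaves in the residual all the variation that baseline would have explained, so the interval is wider than it need be.

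At stake is the precision of the effect estimates, which are a main quantitative product of a trial meant to inform a larger one.

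**Working it through.** **The plan's own figure.** With 17 randomised per arm and about 10% dropout, 17 × 0.9 = 15.3 remain; conversely 15 / 0.9 = 16.7, rounded up to 17. The expected 15 per arm is reproduced and is used below.

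**Inputs.** From the protocol article: three arms, 1:1:1 allocation, 15 evaluable per arm, 95% intervals (two-sided 5% taken as implied). Assumed, because the article gives none: the baseline-outcome correlation r (0.3, 0.5, 0.7), an illustrative effect of 0.8 SD, normal data, and the meaning of *relevant*.

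**Closed form.** Adjusting for baseline multiplies the residual variance by about 1 − r². Fifteen adjusted patients per arm are then worth about 15 / (1 − r²) unadjusted ones:

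- r = 0.3: 15 / 0.91 = 16.5
- r = 0.5: 15 / 0.75 = 20
- r = 0.7: 15 / 0.51 = 29.4

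**Simulation.** 20,000 three-arm trials per setting were analysed by least squares with group terms, with and without baseline. Without adjustment the mean 95% CI half-width for a pairwise difference is 0.73 SD and power at 0.8 SD is about 57%. Always adjusting lowers the half-width to 0.71, 0.64 and 0.53 SD at r = 0.3, 0.5 and 0.7, and raises power to about 60%, 68% and 84%.

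Under the conditional rule the result depends on the reading of *relevant*:

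| Reading of *relevant* | Endpoints left unadjusted | Half-width, r = 0.5 (SD) | Power, r = 0.5 | Power, r = 0.7 |
|---|---|---|---|---|
| Baseline F-test p<0.05 | about 95% | 0.73 | 58% | 59% |
| Baseline F-test p<0.10 | about 90% | 0.73 | 58% | 60% |
| Any two arms differ by >0.5 SD | 63–68% | 0.70 | 61% | 67% |
| Any two arms differ by >0.2 SD | 15–17% | 0.66 | 66% | 80% |
| Always adjust | 0% | 0.64 | 68% | 84% |

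The ranges in the second column cover 15 and 17 per arm; the other columns are for 15. A further reading, any difference from control above 0.3 SD, leaves about 37% unadjusted and gives power of about 65% (r = 0.5) and 74% (r = 0.7). Separate simulation runs differ by about one percentage point.

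**Low correlation.** At r = 0.3 the full CI width is about 1.41 SD with adjustment always, against 1.42–1.46 SD under the rule. Break-even lies between r = 0.1 and 0.2. If baseline is uncorrelated with outcome, adjusting costs almost nothing (half-width 0.74 against 0.73 SD).

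**Type I error under the rule.** About 0.040–0.048 at r = 0.5 and 0.030–0.043 at r = 0.7, which is at or below the nominal 0.05.

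**Logistic models.** With an outcome dichotomised from the same data (15 per arm, 0.8 SD effect), adjustment widened the median 95% interval on the log odds ratio scale from 3.1 to 3.6 (r = 0.5) and from 3.1 to 4.2 (r = 0.7), while power rose. The adjusted odds ratio is conditional on baseline and so is a different quantity from the unadjusted one.

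**The case against.** The case on the other side is substantial, and much of it stands.

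- **Most comparisons lose precision.** A reader might infer this. It holds if *relevant* means a significance test or a difference of about 0.5 SD. It fails at 0.2–0.3 SD, where only about 15–37% of endpoints stay unadjusted. The article states no threshold, so the claim cannot be made.
- **False positives are inflated.** A reader might infer this too. Type I error of 7.5–8.8% arises if an analyst fits both models and keeps the more favourable one (r = 0.5 and 0.7). Section 2.7 describes nothing of the kind: its trigger is the baseline values, not the results. Sections 2.4.5 and 3.1 also keep the data analysts blinded to group assignment, which makes steering towards a treatment harder.
- **The threshold may be in the analysis plan.** A missing definition is something an article can leave to a fuller document, so it carries no weight by itself. The conditional principle is stated in the article, and a definition elsewhere would not repair it.
- **Not every outcome has a baseline.** Global impression of change and ratings of therapy success have none, and the condition on availability deals with these properly.
- **The trial is exploratory.** All p-values are labelled so, there is no sample size calculation, and group means and SDs are reported in any case. This lowers the severity. It does not explain why information already collected should be set aside.

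**Conclusion.** The point holds for continuous outcomes with a measured baseline. Conditioning adjustment on observed imbalance makes the model depend on the data, can mix adjusted and unadjusted estimates, and costs precision whenever the baseline term is omitted. With 15 per arm and a 0.8 SD effect, the loss of power against always adjusting is from almost nothing to about 3 percentage points at r = 0.3, about 1 to 10 points at r = 0.5, and about 3 to 24 points at r = 0.7. The lower end of each range belongs to a low threshold for *relevant* and the upper end to a baseline test at p<0.10. Correlation, effect size and threshold are all assumptions; below a correlation of roughly 0.15 nothing is lost.

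The errors of the rule run towards wide intervals and mildly conservative p-values, so the documents do not support a charge of inflated false positives. For logistic endpoints the loss is one of power, not of odds-ratio interval width. This is a change that should be made, not one on which the validity of the trial depends.

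**What to change.** Replace the parenthetical condition in section 2.7 with a fixed rule, for example: *Each model includes treatment group and, where it was measured, the baseline value of the same outcome, whether or not the groups differ at baseline.* Outcomes without a baseline, such as global impression of change, use treatment group only. For logistic models, add that the odds ratio is conditional on baseline. The change should be dated before any data by group are examined.

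The cost is one sentence and one residual degree of freedom per model, with no new data or patients. For logistic endpoints there is also a change in what the odds ratio measures, and its interval may be wider although power is higher.

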### 2.8. Data collection and management

The personally identifiable data are entered and managed in a password-protected MS Access database and serve as a re-identification list. The database resides on a separate project drive, with limited accessibility. Data from the survey instruments are entered in pseudonymized form into a SoSci-Survey online database programmed by the Institute of Social Medicine, Epidemiology, and Health Economics at Charité Universitätsmedizin Berlin, via an HTTPS connection (SSL encryption) with an existing Internet connection to the server, which is located within the Charité IT infrastructure. The data received from the server can be exported for further processing, and this can only be performed by the data manager via a password-protected login. The exported data are stored on a specially protected drive within the server of the Institute of Social Medicine, Epidemiology, and Health Economics.

The questionnaires are entered into the online database in a pseudonymous form by 1 or more persons known by name and authorized by the principal investigator. The entry of the questionnaires is also password protected. After checking for correctness and plausibility, the data are transferred to SPSS data format.

### 2.9. Withdrawal criteria and management

Patients may or must withdraw from the study if the continuation of the study imposes an unreasonable burden on the patient because of the patient condition, if a serious adverse event occurs and a causal relationship is established by the study director, if patients request withdrawal from the study and/or there is a lack of willingness to cooperate or comply, and/or if circumstances arise that make continued participation unreasonable, such as massive deterioration in health due to serious illness.

Reasons and timing of withdrawal will be recorded in standard case report forms and stored in the study database.

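### Section 2.9 makes non-compliance and a related SAE grounds for leaving the study, not only the intervention, so outcomes can be lost and the available-case analysis can depart from intention to treat

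*Protocol article*

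**What the plan says.** Section 2.9 opens with "Patients may or must withdraw from the study" and then lists the grounds. Two matter here: "if a serious adverse event occurs and a causal relationship is established by the study director", and "if patients request withdrawal from the study and/or there is a lack of willingness to cooperate or comply". The text does not say which grounds are mandatory and which are discretionary. No category covers a patient who stops the affusions or acupressure but goes on answering questionnaires. On what is kept at withdrawal, it says: "Reasons and timing of withdrawal will be recorded in standard case report forms and stored in the study database". It mentions no outcome collection after that point.

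Section 2.7 names the intention-to-treat principle and defines the population as "classification according to each randomization group, for patients with the data available for the respective evaluation". On missing values it says: "There will be no substitution for the missing data".

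Outcome questionnaires are due at baseline, week 6 and week 12 (section 2.4.4). Treatment is optional after week 6 (sections 2.4.1 and 2.4.2). The waiting-list arm is followed without study treatment throughout (section 2.4.3).

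**The concern.** Intention to treat needs outcomes from randomised patients whatever they do with their treatment. Section 2.9 states a rule under which unwillingness to continue the treatment can end participation in the study, and section 2.7 then has nothing to analyse for that patient. The label of the randomised group is kept, but the outcome may be missing because of behaviour after randomisation.

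Refusing daily affusions or acupressure can arise only in the two active arms, so this route of loss falls mainly on them. The trial is meant to inform feasibility and the sample size of a confirmatory trial (section 1.2). Patients who give up the intervention bear on both, and outcomes that were never collected cannot be recovered at analysis.

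**Working it through.** **The two sections side by side**

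- Withdrawn for unwillingness or a related SAE before week 6: no week 6 or week 12 questionnaire is foreseen, so the patient is absent from every post-baseline comparison.
- Withdrawn between weeks 6 and 12: counted at week 6, absent at week 12.
- Applies the treatment rarely but returns the questionnaires: stays in the randomised group at both times.
- Unwilling to go on in week 5: may be removed. Stops in week 7: stays, because treatment is then optional.

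The last contrast shows that the design already follows untreated patients, so nothing in it requires the loss.

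**The plan's own figure**

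Inputs from section 2.5: about 10% dropout before week 12, 17 randomised per group, at least 15 expected per group at week 6. 15 / 0.9 = 16.7, rounded up to 17; 17 × 0.9 = 15.3; 3 × 17 = 51. The figure reproduces. The 10% covers all causes and sets no share aside for non-compliance or SAEs.

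**Possible size (assumptions)**

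The article gives no effect size, SD or rate of such withdrawals. Let a share w of an active arm be withdrawn, with outcomes worse by g than the rest of that arm. Let a share v of the waiting-list arm be lost, with outcomes worse by h than the rest of that arm. Then:

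available-case difference − all-randomised difference = w·g − v·h

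If withdrawn patients gain nothing and otherwise resemble the rest, g equals the effect in compliers, δ. With v = 0 the all-randomised effect is δ(1 − w), and the ratio is 1/(1 − w):

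- w = 5%: 1/0.95 = 1.05
- w = 10%: 1/0.90 = 1.11
- In whole patients: one of 17 gives 17/16 = 1.06; two of 17 give 17/15 = 1.13
- w = 20% or 30%: 1.25 or 1.43, but both shares exceed the total dropout that the plan expects

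**Direction**

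Take δ = g = 0.5 SD and w = 10% (assumed):

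- v = 0: 0.05 − 0 = +0.05 SD
- v = 10%, h = 0.5 SD: 0.05 − 0.05 = 0
- v = 20%, h = 0.5 SD: 0.05 − 0.10 = −0.05 SD

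**Against the imprecision**

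With 15 per group, the 95% interval for a two-group difference has a half-width of 2.05 × √(2/15) = 0.75 SD. A shift of 0.05 SD is small beside that.

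**Carried into a later trial**

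With two-sided 5%, 80% power and the normal approximation (all assumed), n per arm = 2(1.96 + 0.84)²/δ². For δ = 0.5 this gives 63; for 0.5 × 0.9 = 0.45 it gives 78.

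**The case against.** The strongest reply has four parts.

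- **The rule is softer than it looks.** The wording leaves discretion, and the ground is unwillingness, not a low number of applications. Diaries record frequency, telephone calls in weeks 1 and 3 deal with difficulties, and the interventions can be adjusted. A reader might infer that all non-adherers leave the data set and that this is a completer analysis. The documents do not support that: infrequent users who return questionnaires stay in, and section 2.7 openly describes an available-case analysis at each time point. This part stands.
- **Loss is not confined to the active arms.** Unwillingness to cooperate can also concern questionnaires and diaries, which waiting-list patients complete too. Section 3.1 expects patients who do not receive the desired intervention to be lost more often. A reader might infer a bias in favour of the interventions, but the net direction is not established. This part stands.
- **Information on these patients survives.** Sections 2.6 and 2.9 record reasons for dropout, and section 2.10.1 makes no exception to SAE reporting for withdrawn patients. A reader might infer that safety follow-up ends at withdrawal, but the article does not say so. Reasons for dropout, however, do not replace the missing outcomes.
- **An article condenses the full protocol.** Detail on follow-up after withdrawal may be given there. This does not dispose of the point, because the article states the rule itself: non-compliance is named as a ground for leaving the study.

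**Conclusion.** The point holds in limited form. Section 2.9 does not distinguish stopping the self-treatment from leaving data collection. Together with the available-data rule in section 2.7, it allows outcomes to be lost because of post-randomisation behaviour, mainly in the active arms. That can undercut the stated intention-to-treat principle.

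The size cannot be computed from the document. An overstatement of about 11% follows only if the whole planned 10% dropout in an active arm is of this kind, those patients gain nothing, and no offsetting loss occurs among controls. Larger figures need more dropout than the plan expects. The distortion would be small beside the imprecision of 15 patients per group, but it could carry over into the planning of the next trial.

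The trial is exploratory, with unadjusted exploratory p-values and no confirmatory hypothesis. This should be fixed, but it does not invalidate the trial.

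**What to change.** In section 2.9:

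1. Separate discontinuation of the study intervention from withdrawal from the study. Leave the existing clinical grounds unchanged as reasons to stop the intervention; this point takes no position on them.
2. Remove lack of compliance with the intervention as a ground for study withdrawal.
3. State that patients who stop the intervention are still asked for the week 6 and week 12 questionnaires and the safety documentation, and are analysed in their randomised group, unless they withdraw consent or cannot provide data.

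The cost is a short amendment, an instruction to staff and some extra follow-up contact. The questionnaires are already scheduled and the sample size of 17 per group does not change. The change has to be made while patients are still being followed.
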